### Interventions

#### Arm 1: eHealth self-management support programme

This programme consists of two parts. First, participants will complete a PSE programme. We assume that when participants finish the educational programme, they will be able to apply the learnt information and will be motivated to be more physically active despite barriers such as pain and fatigue. However, there is often an intention-behaviour gap. For that reason, the second part of the self-management programme consists of a goal and self-regulation programme based on the HAPA to promote an active lifestyle. Combining both PSE and PA behaviour change approaches, the key features of the eHealth self-management support programme under investigation in this project include:

Accessibility from any digital device (laptop, tablet, smartphone) after receiving a personal login code provided by the researcher. The eHealth programme is accessible for the whole duration (ie, 1 year) of the study.After going through an instruction page, participants go through the eHealth programme independently at their own pace. It is recommended to do the PSE part in 6 weeks and the PA coaching in 6 weeks leading to a recommended total duration of 12 weeks.A chatbot goes into a conversation with the participant about persistent pain symptoms and PA. Based on targeted questions (by means of an underlying decision-tree-based algorithm created in the development phase of the project and informed by expert knowledge^45^), automated and personalised information is given about pain mechanisms and pain self-management tips. Short videos, images, external website links, reflection questions and quizzes are incorporated to address various learning styles and enhance engagement throughout the programme.Twenty-five different modules (see online supplemental appendix B) on different topics related to persistent pain after cancer treatment are presented according to the responses of the participants to questions within the chatbot. This way, there is a logical flow through the modules without unnecessary information being provided (eg, information about pain after chemotherapy, if the survivor has reported having no chemotherapy). The different modules are also freely accessible at all times in the main menu of the programme, when completed. Each module takes 5–30 min. The goal is to go through all information (±3 hours) over a maximum of 6 weeks. The feasibility and acceptability of this educational part of the eHealth programme were demonstrated in a pilot study by De Groef *et al*.^45^As part of promoting PA, after receiving the relevant PSE, participants go through a goal and self-regulation programme based on the HAPA model to promote PA.^46^,^48^ The programme consists of a daily cycle: each morning, participants are automatically directed towards the ‘goal’ module (‘goal setting’), in which they are requested to set a specific step or activity goal (‘action planning’), considering the anticipated possibilities or obstacles of that day (‘coping planning’). They have the possibility to select or formulate specific actions within four domains (transport, household, work/school, leisure time). Participants formulate the degree of difficulty of performing the action plan and how to cope with these difficulties. In the evening, the users are asked to reflect on their daily action plan by writing down barriers and facilitators (‘review behavioural goal’, ‘discrepancy between current behaviour and goal’). Participants can monitor their progress towards their daily goal (‘self-monitoring’) by using a step counter (watch or smartphone). This segment of the eHealth programme consists of three phases, each lasting 5 to 7 days, followed by a fourth phase that remains open and can be used on request. Throughout these four phases, the use of the full goal and self-regulation cycle fades out, prompting skills learning and programme-independent use of self-regulation techniques. This part of the eHealth programme is based on the eHealth programme MyDayPlan developed and tested before by the research team.^49^,^51^ This MyDayPlan intervention, based on the HAPA model, has already been found to be effective in altering health behaviours such as PA and dietary behaviour in diverse populations and diverse conditions, including chronic conditions.^49^,^51^The programme is a stand-alone programme that a patient can use independently. To improve outreach and sustained use of the intervention, reminders by email are provided in the first three phases.As part of the eHealth programme, participants can be advised to consult the healthcare provider that recruited the patient (eg,general practitioner, oncologist, anaesthesiologist). To maintain the pragmatic nature of the trial, the healthcare provider decides whether an additional consultation is needed for the particular patient (individually tailored).

#### Arm 2: Usual care

Currently, in Belgium, the standard care provided to breast cancer survivors experiencing persistent pain primarily involves a pharmacological approach and general advice regarding PA, lifestyle and psychological support.^52^ The hospitals typically distribute general brochures containing information on the long-term side effects of cancer treatments, alongside specific brochures advising individuals on how to manage pain and suggesting consultation with healthcare providers when necessary. To streamline this information, a study-specific brochure has been created to summarise available resources. Participants in this trial arm receive this study-specific brochure sent by postal mail. Consequently, participants allocated to the usual care group will not engage in any formal PSE and/or PA programmes with a physical therapist as part of this project. Although there are no restrictions placed on their ability to pursue self-initiated care or engage in PA.

#### Arm 3: Face-to-face self-management support programme

The face-to-face self-management support programme consists of the same two parts as the eHealth intervention: a PSE module, combined with an active behavioural approach, that is, a PA coaching module (24–27). The programme includes nine individual face-to-face sessions over the course of 12 weeks, each lasting 30 min, in line with the regulations of the Belgian Healthcare system. The intervention is delivered by a physical therapist in primary care who has been recruited and trained by the research team.

In the first session, a biopsychosocial assessment is performed, and an introduction to the PSE provided in sessions two and three is given.The content of the PSE programme in sessions two and three is the same as for the eHealth programme. Like the eHealth programme, this education intervention includes advice for activity management while experiencing pain and other symptoms, in order to remove barriers for an active lifestyle. The educational information is presented both verbally (explanation by the therapist) and in written form (a brochure with summaries, pictures, metaphors and diagrams).In the fourth session, the physical therapist discusses the participant’s current behaviour regarding an active lifestyle. Principles such as graded activity or activity pacing will be discussed based on necessity.The fifth session focuses on setting appropriate goals for achieving an adaptive active lifestyle.During sessions six through nine, the physical therapist coaches and empowers the participant by reflecting on goals, discussing barriers and facilitators, setting new goals and revising concepts discussed in education as necessary.

All physical therapy sessions are reimbursed by the health insurance of the participant. The personal share of the participant will be reimbursed by the project.

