### Sample size

This study adopts a three-arm design to evaluate the eHealth intervention’s superiority to usual care and non-inferiority to face-to-face intervention using a hierarchical testing procedure.^63^ The trial will be termed successful if superiority of the eHealth intervention to usual care as well as non-inferiority of the eHealth intervention to the face-to-face intervention has been shown. A hierarchical testing procedure will be applied, first testing superiority, followed by testing non-inferiority if and only if superiority was shown. Consequently, no correction for multiple testing needs to be applied. Note that if superiority was shown, but showing non-inferiority failed, it is still allowed to conclude that eHealth intervention is effective, but not that it can replace the face-to-face intervention.

The primary outcome used to test superiority as well as non-inferiority is the PDI measured at 6 months. Both tests will be based on the comparison of the mean value after correction for the baseline PDI (Analysis of Covariance (ANCOVA) approach). The assumed SD of the PDI and the correlation between baseline and 6 months equal 15 and 0.65, respectively, and were obtained from pilot data on 28 subjects.^45^ No difference in PDI was expected between face-to-face and eHealth self-management and the region of non-inferiority was defined as a difference of five PDI points. The sample size was calculated to have at least 80% power to show non-inferiority based on a one-sided test with alpha equal to 0.025 (hence, equivalent to a two-sided test with alpha=0.05). A simulation study with 2000 simulations was used, and the power was defined as the percentage of sampled datasets where non-inferiority has been shown using the ANCOVA approach. With 79 subjects in the eHealth and the face-to-face group, there is at least 80% power to show non-inferiority.

To show superiority of eHealth intervention vs usual care based on a two-sided (ANCOVA) test with alpha equal to 0.05, 83 subjects per group are required to detect with at least 80% power a difference of 5 points. Note that having at least 80% power for each of the two comparisons separately does not guarantee 80% power simultaneously.

Strictly speaking, fewer patients are required in the face-to-face group compared with the two other groups. However, given the small difference (79 vs 83), it was decided to recruit an equal number of patients in each of the three groups.

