### Data analysis

A constrained longitudinal data analysis model (cLDA) will be used to compare the PDI between the three groups.^65^ In the cLDA, both the baseline and post-baseline values (12 weeks, 6 months and 12 months) are modelled as dependent variables, as opposed to a (longitudinal) ANCOVA model in which the baseline value is included as a covariate. Although the baseline measure is included in the response vector in cLDA, the true baseline means are constrained to be the same for different treatment groups due to randomisation, and this analysis provides an adjustment for the observed baseline difference in estimating the treatment effects. As opposed to the ANCOVA model, the cLDA approach can handle the presence of missing data and produces unbiased estimates if the missing data mechanism is missing at random. Additionally, 95% CIs for the group-specific mean post-baseline values will be constructed as well as the confidence intervals for the differences between the groups. The stratification variable will be added as a fixed factor in the model.

The primary analysis refers to the comparison after 6 months. A hierarchical testing procedure will be applied for the two primary comparisons. First, the difference between the eHealth intervention and usual care will be tested based on a two-sided test with alpha set at 0.05. If significant, non-inferiority of the eHealth intervention vs the face-to-face intervention will be tested based on a one-sided non-inferiority test with alpha set at 0.025 and defining the margin of non-inferiority as a difference of 5 PDI points. For the superiority comparison, the analysis will be based on the intention-to-treat principle, that is, all randomised patients will be analysed in the allocated group. However, for the non-inferiority comparison, the analysis will be based on the as-treated analysis set.

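### Therapists deliver only the face-to-face arm, yet neither the stated sample size nor the stated model allows for possible therapist clustering in the non-inferiority comparison

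*Protocol article*

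**What the plan says.** The face-to-face arm depends on people. Under Arm 3, "The programme includes nine individual face-to-face sessions over the course of 12 weeks, each lasting 30 min", and "The intervention is delivered by a physical therapist in primary care who has been recruited and trained by the research team". The first three sessions cover assessment and pain education; the later ones are individual work on activity, goals and barriers. The eHealth arm has no such provider: "The programme is a stand-alone programme that a patient can use independently". Usual care receives a posted brochure.

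The Sample size section takes these inputs for the Pain Disability Index (PDI): "The assumed SD of the PDI and the correlation between baseline and 6 months equal 15 and 0.65, respectively". It continues: "No difference in PDI was expected between face-to-face and eHealth self-management and the region of non-inferiority was defined as a difference of five PDI points". Its target is "at least 80% power to show non-inferiority based on a one-sided test with alpha equal to 0.025", and the result is: "With 79 subjects in the eHealth and the face-to-face group, there is at least 80% power to show non-inferiority". Superiority needs 83 per group, all arms are made equal, and 7% dropout brings each to 90. No ICC, number of therapists, caseload or design effect is stated.

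The Data analysis section names a constrained longitudinal model (cLDA) and one further term: "The stratification variable will be added as a fixed factor in the model". That variable is recruitment setting (Allocation and randomisation section), not therapist. The same model, with a non-inferiority test, serves the key secondary outcome, the Survey of Pain Attitudes (SOPA).

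**The concern.** Participants coached by the same therapist share whatever that therapist does well or badly, so their outcomes may be correlated. Here this can happen in one arm of the comparison only. Treating these participants as independent then understates the variance of the face-to-face mean, and the confidence interval for eHealth minus face-to-face comes out too narrow.

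In a non-inferiority test that error favours a false claim. Non-inferiority is half of the trial's success definition, and by the Sample size section it is what would support the statement that eHealth can replace the face-to-face programme. The planned power for it would also be overstated.

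**Working it through.** **Inputs from the Sample size section.** SD 15, baseline to 6-month correlation 0.65, margin 5, true difference 0, one-sided alpha 0.025. The planned analysed number is 83 per arm.

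**Inputs not in the documents, so assumed.** Number of therapists (10, 20, 40, with equal caseloads) and therapist ICC on the baseline-adjusted scale (0.02, 0.05, 0.10).

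**Step 1: the plan's own figures, without clustering.**
- Residual SD = 15 × √(1 − 0.65²) = 11.40.
- Required n per arm = 2 × 11.40² × (1.960 + 0.842)² / 5² = 81.6, so 82. The margin and the superiority difference are both 5, so the same formula covers both tests. The stated 83 reproduces.
- At 83 per arm: SE = 11.40 × √(2/83) = 1.769; 5/1.769 = 2.826; power = Φ(2.826 − 1.960) = 80.7%.
- At 79 per arm: SE = 1.814; power = Φ(2.757 − 1.960) = 78.7%. The quoted 79 is thus slightly short before any clustering, which is a separate and smaller matter. The plan's 2000 simulations carry a Monte Carlo standard error of √(0.8 × 0.2/2000), about 0.9 points. The rest of the working uses 83.

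**Step 2: clustering in the face-to-face arm only.**
- Caseload m = 83 / number of therapists.
- Design effect in that arm: DE = 1 + (m − 1) × ICC.
- True variance of the difference relative to the unadjusted one: R = (1 + DE)/2.
- Actual one-sided type I error of the unadjusted test at the margin: 1 − Φ(1.960/√R).
- Power with the correct SE: Φ(2.826/√R − 1.960).

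Example, 10 therapists and ICC 0.05: m = 8.3; DE = 1 + 7.3 × 0.05 = 1.365; R = 1.183; √R = 1.087. Type I error = 1 − Φ(1.802) = 3.6%. Power = Φ(2.598 − 1.960) = 74%.

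| Therapists (m) | ICC | DE | One-sided type I, unadjusted | Power, correct SE |
|---|---|---|---|---|
| 40 (2.1) | 0.02 | 1.02 | 2.6% | 80.3% |
| 40 (2.1) | 0.05 | 1.05 | 2.7% | 79.6% |
| 20 (4.2) | 0.02 | 1.06 | 2.7% | 79% |
| 20 (4.2) | 0.05 | 1.16 | 3.0% | 78% |
| 20 (4.2) | 0.10 | 1.32 | 3.4% | 75% |
| 10 (8.3) | 0.02 | 1.15 | 2.9% | 78% |
| 10 (8.3) | 0.05 | 1.36 | 3.6% | 74% |
| 10 (8.3) | 0.10 | 1.73 | 4.7% | 68% |

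**Step 3: break-even point.** 80% power needs 2.826/√R ≥ 2.802, so R ≤ 1.0173 and (m − 1) × ICC ≤ about 0.035. At ICC 0.02, three participants per therapist (2 × 0.02 = 0.04) already exceed it.

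All figures use normal approximations. Power under a small-sample degrees-of-freedom method would be somewhat lower when therapists are few.

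**The case against.** The strongest reply is that the effect is conditional and the document does not settle the condition. Recruitment runs through two hospitals, general practices in Flanders and self-referral, and sessions take place in primary care, so many therapists with one or two participants each are plausible. Common content, written material and central training, with the endpoint about three months after the 12-week programme ends, may also keep the ICC low. With 40 therapists the effect is negligible. This stands: a reader might infer that the standard error is certainly too small and power certainly well below 80%, and the article does not support that. The 68% figure needs both few therapists and a high ICC.

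Second, the article is condensed and a separate analysis plan may add a therapist term. This also stands in part. The article does not rule such a term out, so one cannot conclude that the final analysis will ignore therapist. A later plan cannot, however, put a clustering allowance into a sample size already fixed here. The SD and correlation would not supply one either: they come from a 28-subject pilot, which the Arm 1 section describes as covering the educational part of the eHealth programme.

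Third, a reader might infer that therapist identity is not being recorded. Nothing shows that. The process evaluation measures delivery and dosage, and the project reimburses participants' share of session costs, so the information may already exist.

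Fourth, the shortfall at 79 per group is not evidence of clustering; it appears with independent observations.

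**Conclusion.** The point holds in conditional form, as a cheap improvement. The non-inferiority comparison is partially nested, and neither the stated sample size nor the stated model terms allow for it. Given shared therapists and a positive ICC, the direction is certain: an interval that is too narrow and a power figure that is too high. The size is not known. Across the assumed range at 83 per arm, one-sided type I error runs from 2.6% to 4.7% against a nominal 2.5%, and power from about 80% down to 68%. With only 0.7 points of slack above 80%, modest clustering is enough to lose the stated power. The eHealth versus usual care comparison is not affected.

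If the wording under Arm 3 meant literally one therapist, therapist and arm would be fully confounded and no model could separate them. A reading with several therapists is more natural.

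**What to change.** 1. Make sure therapist identity for each face-to-face participant is in the analysis data.
2. For eHealth versus face-to-face, on both PDI and SOPA, specify a partially nested model: a therapist random effect on post-baseline values in the face-to-face arm only, arm-specific residual variance, and Satterthwaite or Kenward-Roger degrees of freedom. State in advance what is done if the therapist variance is estimated as zero.
3. Restate non-inferiority power over a range of ICC and caseload, using the actual or expected number of therapists.
4. If one therapist delivers the whole arm, state this as a limit on the conclusion.

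The cost is small: possibly one data field, a modest extension of the model and a short power table. The interval will be slightly wider and the stated power less favourable, and the variance estimate may be zero when clusters are few or small. Recruitment is planned to January 2028, so this can be fixed well before analysis. It does not in itself call for more participants.

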### Outcomes

Assessments will be performed at baseline, after 6 weeks, 12 weeks and 6 and 12 months after baseline. However, because of feasibility limitations and relevance, not all outcome parameters are assessed at each assessment time point. Online supplemental appendix C presents a table with the study outcome measures by assessment time point. Study data will be collected and managed using Research Electronic Data Capture (REDCap) electronic data capture tools hosted at Antwerp University. REDCap is a secure, web-based software platform designed to support data capture for research studies.^53 54^

The primary outcome (primary objective) is pain-related functioning at 6 months post-baseline, assessed using the Pain Disability Index (PDI).^55^ The reliability of the Dutch version is good in the breast cancer population.^56^

As a secondary objective, this research project will determine the effect of the educational part alone of the eHealth self-management programme on pain beliefs and attitudes (key secondary outcome) at 6 weeks (ie, before the start of PA coaching). To determine other *secondary outcomes*, we formulated a programme theory delineating how intervention components, mechanisms and contextual factors of the eHealth programme contribute to intermediate, short-term and long-term results. Employing HAPA as our theoretical framework, we initiated the process by identifying the targeted behaviour (eg, an active lifestyle) and primary outcome (eg, pain-related disability). Subsequently, we identified the necessary steps in the programme and listed the used behaviour change techniques in each of these steps. We also considered contextual factors and possible factors that might hinder or facilitate (moderators) the hypothesised causal chain of mechanisms of change (mediators). Three sessions with health psychologists, physical therapists and behaviour change experts to ensure a thorough development of our programme theory. A mapping of the items of self-reported measures onto constructs relevant to the intervention took place. This allowed us to refine available items, develop new items that were relevant but missing and drop (subscales of) self-reported measures that proved irrelevant according to our programme theory. This approach ensured a comprehensive assessment of patient-related, pain-related, physical and psychosocial outcomes of our programme theory components and outcomes.

For the health-economic analysis, a self-composed questionnaire will be used to determine whether participants are working, working part-time/full-time or working in an adapted work environment. Socioeconomic outcomes will be evaluated using: (1) the Medical Consumption Questionnaire,^57^ a generic instrument for measuring direct medical costs of a patients’ total medical consumption, including additional diagnostics, consultations, surgery including stay in hospitals, physiotherapy, medication and aids prescribed by the general practitioner as well as medication and aids purchased by the patients themselves, and (2) the Productivity Cost Questionnaire^58^ to obtain data regarding the indirect costs outside healthcare, but related to the disease (eg, the costs due to absence of work and possible decreased productivity at a paid job or at an unpaid job). These two questionnaires are understandable, easy to use and generate valid data.^59 60^ The combination of these questionnaires is advised by the Institute for Medical Technology Assessment, Erasmus University Rotterdam (the Netherlands)^61^ and has served in a large number of high-quality cost-effectiveness trials. In addition, a generic health-related quality of life questionnaire, the EuroQol 5-dimension 5-level (EQ-5D-5L) questionnaire, will be administered. With this information, the incremental cost-effectiveness ratio will be calculated as general outcome of economic benefit (cost-effectiveness) and quality-adjusted life-years as outcome of enhanced quality of life (cost-utility analysis).

Parallel to the effectiveness trial, a *process evaluation* will be performed to assess (a) implementation fidelity of the intervention across the three arms, (b) the contextual factors affecting implementation and outcomes, and (c) the determinants of scalability. The design is based on the Medical Research Council guidelines for developing and evaluating complex interventions.^62^ Implementation fidelity will be assessed by measuring delivery, dosage and reach of the intervention (see online supplemental appendix D). Contextual factors affecting implementation and outcomes will be assessed at the nanolevel (patient-health care provider interaction), microlevel (individual healthcare organisation) and mesolevel (collaborative structures for transmural care) through semistructured interviews with patients, healthcare providers and key informant interviews. Scalability of the intervention is considered through its feasibility of integration into routine healthcare processes. Data will be collected through observations and interviews with the key informants and stakeholders at the healthcare organisation level and policy level. These observations and interviews will be organised during and shortly after the intervention.

